Interviews will also be held with patients who declined to take part in the trial to identify reasons for their decision. These interviews will usually be held by telephone to encourage participation. The data gathered will indicate ways to maximise recruitment and to reflect upon how representative individuals in the trial are of other CR patients. About 10 ‘decliners’ will be interviewed early on in the trial.

### Qualitative analysis plan

Data collection and analysis will proceed in parallel. All interview data will be audio-recorded, transcribed verbatim and analysed thematically with the aid of NVivo, and using an approach based on a framework approach [81]. Analysing the data thematically will enable comparisons to be made within and across the interviews, and for the views of staff and patients to be compared and contrasted regarding specific topics, such as intervention acceptability.

## Ethical and governance considerations

The Royal Devon and Exeter NHS Foundation Trust is acting as the trial sponsor. This paper describes the CADENCE study protocol (version 4, 19 June 2015), which was reviewed and a favourable ethical opinion obtained from the National Research Ethics Service (NRES) Committee South West – Exeter (reference: 14/SW/0139) and the relevant NHS research governance approvals were obtained prior to commencing fieldwork from: the Royal Cornwall Hospitals NHS Trust; Somerset Partnership NHS Foundation Trust; Taunton and Somerset NHS Foundation Trust; Torbay and South Devon NHS Foundation Trust; University Hospitals Bristol NHS Foundation Trust; University Hospitals Coventry and Warwickshire NHS Trust; Weston Area Health Trust; and Yeovil District Hospital NHS Foundation Trust. Any protocol amendments will be notified through existing pathways in the UK NRES and NHS research governances system, and the trial team will ensure that all participating CCRPs, staff and patients, and trial registries are informed of any changes to the protocol.

This study is registered with a trials registry (ISRCTN34701576) and has been adopted by the UK Comprehensive Research Network (UKCRN ID: 17105). All researchers and nurses involved in participant recruitment will undertake Good Clinical Practice (GCP) training.

### Data management

All personal information obtained about patients or staff for the purposes of recruitment or data collection will be held in accordance with the UK Data Protection Act, 1998. Each participant will be assigned a research number and all outcome data will be encrypted and stored without the participant’s name or address. Electronic study records will be stored in a SQL server database managed by the Peninsula Clinical Trial Unit (PenCTU), hosted on a secure server maintained by Plymouth University. Access to electronic data will be permission-based, with access to identifiable information limited to those processing questionnaires and performing initial screening activities. Copies of study data retained at participating sites will be securely stored for the duration of the study prior to archiving. Electronic copies of any letters or e-mails sent to study participants will be stored securely on a password-protected computer at the University of Exeter, and paper-based information held in a locked filing cabinet in the research team offices. Names and participant details will not be passed onto any third parties and no named individuals will be included in the write-up of the results. The only time personal information would be passed on to a third party (i.e. the patient’s GP) would be if we considered there to be risk of serious harm to a research participant and safety protocols need to be activated.

All study data will be kept for 10 years under secure conditions on University of Plymouth and University of Exeter servers. We will seek consent from participants for core outcome data from the pilot study to be released in an anonymised form to an independent data repository (for example, the UK Data Archive) following publication of the key planned outcome papers.

### Safety of participants and researchers

While we believe the study has minimal implications for health care staff, participants will have been found to have depressive symptoms and it is, therefore, appropriate to have a safety policy in place regarding the management of potentially serious adverse events (e.g. self-injury or suicidality). The Participant Information Sheet will let the person know that if we are very concerned about their safety or someone else’s safety we may need to break confidentiality and inform their GP.

Involvement in research interviews where participants are asked to reflect on their health issues can, in some cases, cause distress. Should any such difficulties occur during a research interview, the researcher will offer support to the person involved. Should a participant appear significantly upset and at risk as a result of the interview, the researcher will (with permission) advise the individual’s GP of this distress and encourage the person to seek further support from the support network available to them. Should there be any concern that a participant is likely to cause harm either to themselves or another person, their GP will be notified immediately by a senior clinician from the study team. Since researchers will be conducting interviews alone with participants, potentially in the participant’s own home, it will be important to have safeguards in place to protect both participant and researcher. Disclosure and Barring Service checks will be performed on any researcher taking part to ensure that they are an appropriate person to be working with vulnerable adults. To ensure the safety of researcher and patient, a lone-worker policy will be applied, providing a mechanism for ensuring that the exact whereabouts of researchers and patients engaged in research activities is known.

## Project timeline

The project commenced on 1 April 2014 and is scheduled to complete in July 2016. The feasibility study was reported in May 2015. Preparatory work for the pilot trial, including CR team recruitment, commenced January 2015. Cluster randomisation took place in April 2015, and intervention training delivered to the five CR teams in June–July 2015. Participant recruitment commenced July 2015 and is scheduled to complete by the end of 2015. Follow-up data and qualitative interviews will take place between September 2015 and June 2016. Data analysis will commence in January 2016, with the final report due in July 2016.

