**Methods/Design:**

This study tests the uncertainties associated with a large-scale evaluation by conducting an external pilot trial with a nested qualitative study. We aim to recruit and randomise eight comprehensive cardiac rehabilitation teams (clusters) to intervention (embedding enhanced psychological care into routine cardiac rehabilitation programmes) or control (routine cardiac rehabilitation programmes alone) arms. Up to 64 patients (eight per team) identified with depressive symptoms upon initial assessment by the cardiac rehabilitation team will be recruited, and study measures will be administered at baseline (before starting rehabilitation) and at 5 months and 8 months post baseline. Outcomes include depressive symptoms, cardiac mortality and morbidity, anxiety, health-related quality of life and service resource use. Trial data on cardiac team and patient recruitment, and the retention and flow of patients through treatment will be used to assess intervention feasibility and acceptability. Qualitative interviews will be undertaken to explore trial participants’ and cardiac rehabilitation nurses’ views and experiences of the trial methods and intervention, and to identify reasons why patients declined to take part in the trial. Outcome data will inform a sample size calculation for a definitive trial.

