### Study aims and objectives

The overarching aim of this pilot study is to test the methods and procedures required to undertake a fully powered evaluation of the clinical effectiveness and cost-effectiveness of CR teams implementing an enhanced psychological care intervention (EPC) for patients with ‘new onset’ depressive symptoms using CR services compared with CR services delivering usual care. Specific objectives are:To quantify the flow of patients (i.e. eligibility, recruitment and attrition rates) from the cardiac event to the 8-month follow-up for patients entering the CR care pathway, and in particular, to document the flow of those patients who agree to take part in the pilot trialTo collect participant outcome data in order to estimate the standard deviation for continuous outcomes to inform sample size calculations for a definitive trialTo establish the data collection methods required to support a definitive economic evaluationTo gather qualitative evidence from patients (including participants who did or did not adhere to the EPC, and those who declined to take part in the trial) and CR nurses on the acceptability of EPC, and on the appropriateness of study methods and procedures. Information will also be sought on the content of usual psychological care within CR teams

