### Data collection

Participants in both arms will complete baseline measures prior to commencing CCRP, and then two face-to-face follow-up interviews with a researcher at 5 and 8 months post randomisation (Fig. 2). Blinding of patients, practitioners or researchers extracting data on study outcomes is not possible in this cluster design, but the final analysis will be carried out by a statistician who is blind to treatment allocation. Data will be collected on process measures, patient-reported outcomes, and resource use and costs.

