## Trial status

Patient participant recruitment commenced in July 2015 and is ongoing, scheduled for completion in December 2015.

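### The stated calendar closes follow-up in June 2016, but the last 8-month visits fall due at the end of August 2016, so late recruits cannot reach 8 months on schedule

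*Protocol article*

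**What the plan says.** Four statements in the protocol article fix the calendar.

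- Recruitment (Project timeline): "Participant recruitment commenced July 2015 and is scheduled to complete by the end of 2015". The Trial status section agrees: "Patient participant recruitment commenced in July 2015 and is ongoing, scheduled for completion in December 2015".
- Visit times (Abstract, Methods/Design): measures are taken "at baseline (before starting rehabilitation) and at 5 months and 8 months post baseline". The Data collection section uses a different anchor: "two face-to-face follow-up interviews with a researcher at 5 and 8 months post randomisation". The Project timeline adds that "Cluster randomisation took place in April 2015".
- Collection window (Project timeline): "Follow-up data and qualitative interviews will take place between September 2015 and June 2016".
- Project end and final report (Project timeline): July 2016.

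Two further statements show what depends on the 8-month visit. The first objective includes "attrition rates) from the cardiac event to the 8-month follow-up". The Statistical analysis plan section says that outcome completion and drop-out will be reported with 95% confidence intervals. The Sample size section aims for 64 patients in 6 months and gives margins of ±12.8% at a follow-up percentage of 50% and ±9.3% at 90%.

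**The concern.** The recruitment window plus 8 months runs past the date on which data collection stops. Part of the sample then has no scheduled 8-month visit inside the study, however willing those participants are to attend.

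Retention is one of the main things this pilot is meant to measure. If the visits that never fall due are not separated from the visits that were missed, the 8-month completion rate will partly reflect the calendar and not the acceptability of the trial. If they are separated, the 8-month estimate rests on fewer participants than the number recruited, and its precision is lower than the article gives for 64.

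**Working it through.** **1. The article's own precision.** An exact (Clopper-Pearson) 95% interval for 32/64 is 37.2% to 62.8%, a half-width of 12.8 points. For 90%, the lower bound at 58/64 is 80.7%, and 90 − 80.7 = 9.3 points. Both stated margins are reproduced. The normal approximation gives 12.25 and 7.35 and does not match, so the exact method is used below.

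**2. Due dates counted from baseline.**

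| Baseline | 5 months | 8 months |
|---|---|---|
| 1 July 2015 | 1 December 2015 | 1 March 2016 |
| 31 December 2015 | 31 May 2016 | 31 August 2016 |

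Every 5-month visit falls before the end of June 2016. The last 8-month visit falls two months after that and one month after the end of July 2016. Working back, 30 June 2016 less 8 months gives a last usable baseline date of 30 or 31 October 2015, depending on the month-end convention. Reading the June close as 30 June is the reading most favourable to the plan.

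**3. Due dates counted from randomisation.** April 2015 + 5 months = September 2015; April 2015 + 8 months = December 2015. The 8-month point would then fall while recruitment is still open, and the 5-month point before many participants have enrolled. This anchor cannot serve as a follow-up schedule for individuals, so it does not remove the conflict.

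**4. Share affected.** The article gives the window and the target but no accrual pattern, so the pattern is an assumption.

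- Even accrual from 1 July (184 days), with 61 days after 31 October: 61/184 = 33%, and 0.332 × 64 = 21.2. With 30 October as the cut-off: 62/184 = 34%, or 21.6.
- Even accrual from 15 July: 62/170 = 36%. From 31 July: 62/154 = 40%.
- Accrual falling linearly to zero over six months: (2/6)² = 11%. Rising linearly from zero: 1 − (4/6)² = 56%.
- Even accrual from 1 July with visits continued to 31 July 2016: 31/184 = 17%, about 11 participants still missed.

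**5. Consequence under even accrual from 1 July.** The two results below belong to alternative denominators and do not add up.

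- Denominator 64: at most 64 − 21 = 43 can be seen, so completion is capped at 43/64 = 67%. A true retention of 90% would show as about 0.90 × 2/3 = 60%. The interval width is still that of 64.
- Denominator 43 (those who fall due): there is no cap, but the exact interval at 50% (21.5/43, using the continuous form) is 34.4% to 65.6%, a margin of ±15.6 points.

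**The case against.** The conflict between the dates has no answer in the article, but several stronger readings are tempting and go too far.

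- **Late recruits will be counted as drop-outs.** A reader might infer this, but the article states no denominator. The flow diagram is not reproduced in the text at hand, and a full protocol or analysis plan could define one. It is a risk and not a stated rule. Such a document could settle the counting; it could not produce visits due after collection has closed.
- **The September 2015 start is a second error**, since the first 5-month visit is due in December 2015. This is not supported. The sentence covers qualitative interviews as well, and the Qualitative interview study section plans interviews with decliners early in the trial.
- **The ±12.8 margin and the standard deviations for the definitive trial are 8-month quantities.** The Sample size section and the objectives name no time point for either. The stated margin holds at 5 months if all 64 are recruited.
- **One third is a fixed figure.** It rests on even accrual from 1 July.

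It can also be said that a visit window might absorb the gap, since the article states none. A participant enrolled on 31 December 2015 would have to be seen by 30 June 2016, which is 6 months after baseline, so the tolerance would need to be two months. That would no longer be an 8-month measurement.

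Finally, this is a pilot that will not report definitive effectiveness. That limits the consequences for effect estimates, but not for attrition, which is one of its stated objectives.

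**Conclusion.** The point stands as an inconsistency between stated dates. Recruitment to the end of December 2015, outcomes 8 months after baseline, collection closing in June 2016 and a report in July 2016 cannot all hold. That follows from the dates alone, without any accrual assumption.

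The number affected does need one: about 21 of 64 under even accrual from 1 July, and roughly 11% to 56% under the falling and rising patterns. The effect on reporting is conditional on the denominator chosen: either a ceiling near 67% or a margin near ±15.6 points. The 5-month data are not affected.

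**What to change.** Reconcile four items: the end of recruitment, the close of follow-up, the report date, and the follow-up anchor (baseline in the Abstract, randomisation in Data collection). Then take one of two routes.

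1. **Extend.** Continue 8-month collection to 31 August 2016 and move the report. This costs about two more months of fieldwork and a later report, with no extra patients.
2. **Keep the close and define the denominator.** Suggested wording: 8-month completion and drop-out are calculated among participants whose 8-month date, counted from baseline, falls on or before the close of data collection; other participants are shown as not yet due in the CONSORT flow and are not counted as lost. Restate the expected 8-month number and its precision (about 43 and ±15.6 points at 50% under even accrual). This is a change of wording only; its price is a less favourable 8-month precision.

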## Discussion

This paper presents the study protocol (version 4, 19 June 2015) for the CADENCE study, reported to satisfy the Standard Protocol items: Recommendations for Interventional Trials (SPIRIT) guidelines (Additional file 2). This study will provide important information supporting the development and subsequent evaluation of psychological treatment for patients identified with depressive symptoms following an ACS or revascularisation procedure. Our EPC intervention involves training CR nurses in the application of evidence-based mental health care co-ordination algorithms, and in how to actively support and monitor patients working through a BA self-help manual with associated tasks. While both mental health care co-ordination and BA have previously been demonstrated to be effective treatments for patients with depression, their application to busy CR settings and patients is untested. A crucial element of this research will be to examine the feasibility and acceptability of implementing mental health care management strategies within the routine care. Study outcomes will inform the design of a definitive clinical trial that will provide evidence of the effectiveness, cost-effectiveness and acceptability of embedding psychological care within the CR care pathway.

This study was funded in response to a commissioning brief from the Health Technology Assessment board of the UK the National Institute for Health Research (NIHR; project reference 12/189/06), which identified this research area as an important knowledge gap and which sought to investigate an intervention embedded within routine care. We will disseminate our findings widely, to ensure this research will guide policy-makers and clinicians in the future development and organisation of psychological care for patients with depressive symptoms engaging with CR services. We anticipate that data on acceptability will be of immediate interest to patients and their families, professionals responsible for the design and implementation of CR services, and to the professional body (BACPR) responsible for defining core services and standards of care within NHS CR services.

## Trial status

Patient participant recruitment commenced in July 2015 and is ongoing, scheduled for completion in December 2015.

## Abbreviations

ACS: acute coronary syndrome
ADM: antidepressant medication
AE: adverse event
BA: behavioural activation
BACPR: British Association for Cardiovascular Prevention and Rehabilitation
BADS-SF: Behavioral Activation for Depression Scale – Short Form
BDI-II: Beck Depression Inventory
BMI: body mass index
CABG: coronary artery bypass grafting
CBT: cognitive behavioural therapy
CIS-R: revised clinical interview schedule
CR: cardiac rehabilitation
CRRP: comprehensive cardiac rehabilitation programme
CSQ-8: Client Satisfaction Questionnaire (CSQ-8)
EQ-5D: EuroQoL Index
FFT: Friends and Family Test
GP: general practitioner
IAPT: Improving Access to Psychological Therapies
ICC: intra-cluster correlation coefficient
MI: myocardial infarct
MICD: minimally important clinical difference
NHS: National Health Service
NICE: National Institute of Clinical Excellence
NIHR: National Institute for Health Research
PCI: percutaneous coronary intervention
PHQ-9: Patient Health Questionnaire-9
PPI: patient and public involvement
SAE: serious adverse event
SRUQ: Service and Resource Use Questionnaire
